## Abstract

**Background:**

The prognosis for patients with advanced FIGO stage III epithelial ovarian cancer remains poor despite the aggressive standard treatment, consisting of maximal cytoreductive surgery and platinum-based chemotherapy. The median time to recurrence is less than 2 years, with a 5-years survival rate of -20-25%. Recurrences of the disease occur mostly intraperitoneally.

Ovarian cancer is a radiosensitive tumor, so that the use of whole abdominal radiotherapy (WAR) as a consolidation therapy would appear to be a logical strategy. WAR used to be the standard treatment after surgery before the chemotherapy era; however, it has been almost totally excluded from the treatment of ovarian cancer during the past decade because of its high toxicity. Modern intensity-modulated radiation therapy (IMRT) has the potential of sparing organs at risk like kidneys, liver, and bone marrow while still adequately covering the peritoneal cavity with a homogenous dose.

Our previous phase I study showed for the first time the clinical feasibility of intensity-modulated WAR and pointed out promising results concerning treatment tolerance. The current phase-II study succeeds to the phase-I study to further evaluate the toxicity of this new treatment.

**Methods/design:**

The OVAR-IMRT-02 study is a single-center one arm phase-II trial. Thirty seven patients with optimally debulked ovarian cancer stage FIGO III having a complete remission after chemotherapy will be treated with intensity-modulated WAR as a consolidation therapy.

A total dose of 30 Gy in 20 fractions of 1.5 Gy will be applied to the entire peritoneal cavity including the liver surface and the pelvic and para-aortic node regions. Organ at risk are kidneys, liver (except the 1 cm-outer border), heart, vertebral bodies and pelvic bones.

Primary endpoint is tolerability; secondary objectives are toxicity, quality of life, progression-free and overall survival.

**Discussion:**

Intensity-modulated WAR provides a new promising option in the consolidation treatment of ovarian carcinoma in patients with a complete pathologic remission after adjuvant chemotherapy. Further consequent studies will be needed to enable firm conclusions regarding the value of consolidation radiotherapy within the multimodal treatment of advanced ovarian cancer.

**Trial registration:**

Clinicaltrials.gov: NCT01180504

## Background

Ovarian cancer has the highest mortality rate of all gynaecologic cancer in the western world. Symptoms tend to be vague; hence the disease is often detected late. 75% of patients present with advanced stage disease, after it has spread into the peritoneal cavity (stage FIGO III). Despite the aggressiveness of the current standard treatment, consisting in maximal cytoreductive surgery and adjuvant combination chemotherapy (carboplatin and taxane), the prognosis for patients in a stage FIGO III disease remains poor. The median time to recurrence is less than 2 years. Typically recurrences occur intraperitoneally, distant metastasis appear mostly later in the course of the disease. The 5-year survival rate for stage FIGO III disease is approximately 20-25% [1-5]. Various sorts of consolidation therapy have been studied in a series of clinical trials, but yet none has shown to improve survival in ovarian cancer [6-8].

The use of whole abdominal radiotherapy (WAR) as a consolidation therapy would appear to be a logical strategy given that ovarian cancer is a radiosensitive tumor. The fact that WAR can be curative in certain groups of patients has been shown by intensive studies by Dembo et al [9,10]. However, the role of radiation therapy in ovarian cancer remains controversial. In the 1950s, surgery and adjuvant WAR were the dominant treatment modalities [9,10]. Since the improvements of chemotherapy, which gives primarily high response rates and has a systemic effect, radiotherapy has been increasingly abandoned [11].

WAR as a consolidation concept after surgery and chemotherapy has been evaluated in a number of small and non-randomized studies with contradictory results [12-17]. The recent randomized trial of Sorbe indicated that WAR may have a place in the treatment of advanced ovarian carcinoma in patients with complete pathologic remission after adjuvant chemotherapy [18]. A potential benefit was noted regarding the rate of recurrence and progression-free as well as overall survival rates. These results are supported by other small recent series [15,19-23]. It seems that 30 Gy delivered to the whole abdomen can eliminate residual microscopic disease in 45-50% of the cases [15].

However, there are many reasons why consolidation WAR fell into disfavour. It is associated with a high rate of severe acute side effects, particularly myelosuppression, due to additive toxicities after chemotherapy, which often leads to delayed or incomplete radiotherapy [16]. WAR is ineffective for patients with macroscopic disease residuum after chemotherapy [24]. Using the conventional technique, WAR is not able to deliver adequate radiation doses to the upper abdomen, due to limiting organs at risk (OAR), especially liver and kidneys [9]. Eventually WAR is unpopular because of the late bowel toxicity, which is surgically difficult to manage.

As a consequence, during the past decade, WAR has been almost totally excluded from the treatment of advanced ovarian. However, toxicity can now be managed by modern radiotherapy techniques using intensity-modulated radiotherapy (IMRT), which allow a very precise irradiation of complex target volumes while sparing organs at risk like kidneys, liver, and bone marrow [25-29].

Our previous phase I study showed, for the first time, the clinical feasibility of intensity-modulated WAR in combination with modern chemotherapy and surgery and pointed out promising results concerning treatment tolerance [26,30,31]. Ten patients with optimally debulked ovarian cancer FIGO stage IIIc were treated with intensity-modulated WAR up to a total dose of 30 Gy in 1.5 Gy fractions as a consolidation therapy after adjuvant carboplatin/taxane chemotherapy. Treatment was delivered using IMRT in step-and-shoot technique (n = 3) or helical tomotherapy technique (n = 7). The planning target volume (PTV) included the entire peritoneal cavity and the pelvic and para-aortic node regions. Organs at risk (OARs) were kidneys, liver, heart, vertebral bodies and pelvic bones.

Intensity-modulated WAR rendered an excellent coverage of the entire peritoneal cavity including frequent sites of abdominal recurrence like the liver capsule and the diaphragm as well as of the pelvic- and para-aortic node regions. An effective sparing of liver, kidneys and bone marrow allowed delivering the treatment as planned, with a high compliance of patients. Radiotherapy was well tolerated, no severe acute side effects CTC grade 4 occurred. CTC grade 3 toxicities were: diarrhea (n = 1), thrombocytopenia (n = 1) and leukopenia (n = 3). After a median follow-up of 23 months, 4 patients had a tumor recurrence (intraperitoneal progression n = 3, hepatic metastasis n = 1). Small bowel obstruction due to adhesions occurred in 3 patients, 2.5, 3 and 13 months respectively after radiotherapy.

We initiated the current phase-II study to further evaluate toxicity and outcome of intensity-modulated whole-abdominal radiotherapy. The primary objective of the OVAR-IMRT-02 trial is to demonstrate the good tolerability this intensive multimodal adjuvant treatment in a cohort of 37 patients with advanced ovarian-cancer FIGO stage III, optimally debulked and with a complete remission after chemotherapy. Secondary objectives are rate of therapy stop, rate of therapy interruption, rate of acute toxicity, rate of late toxicity, rate of relapse-free survival, rate of overall-survival and quality of life (EORTC-QLQ30).

## Methods/design

### Study design

The OVAR-IMRT-02 is designed as a single-center one arm prospective phase II trial. In order to accelerate the data collection we plan to associate a second study center. Patients fulfilling the inclusion criteria will be treated with intensity-modulated WAR up to a total dose of 30 Gy in 1.5 Gy fractions within a consolidation concept. Thirty seven patients are planned to be enrolled.

### Study objectives

The aim of the study is to demonstrate superior tolerability of consolidating intensity-modulated WAR compared to the conventional technique.

To get an impression of the tolerability of current radiation approaches, we explored the results from historical data on conventional radiation procedure. Adjuvant WAR using the conventional technique after radical surgery and chemotherapy showed a high rate of acute side effects (especially hematotoxicity, but also nausea, vomiting and diarrhoe). The pronounced acute toxicity, which is described in the literature as "severe", leads in many cases to a stop (10-15%) or to an interruption (15-30%) of the therapy and with it to a reduction of its efficacy [22,23,32,33]. This is one of the reasons why WAR is no longer applied. Within the OVAR-IMRT-01 Study, none of the 10 patients showed an acute toxicity CTC grade 4 (0%), and the CTC grade 3 toxicity rate was 40%.

Primary outcome variable of the OVAR-IMRT-02 Study is the tolerability of therapy, defined by the non-occurrence of CTC grade 4 toxicity during the radiation therapy and until 6 weeks after its termination.

Secondary outcome variables are the rate of therapy stop, rate of therapy interruption, rate of acute toxicity, rate of late toxicity, rate of relapse-free survival, rate of overall survival and quality of life (EORTC-QLQ30).

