## Statistical Design and Methods

The primary endpoint of the trial is the tolerability rate, which is calculated as the percentage of patients for which no CTC Grade 4 toxicity occurs during the radiation therapy and until 6 weeks after its termination. The target tolerability rate is 90%, and a tolerability rate of less or equal to 70% is considered to be not of interest. Denoting the tolerance rate by *p*, the related test problem can be formulated as *H*_*0*_: *p *≤ *p*_*0 *_= 0.70 versus *H*_1_: *p *≥ *p*_1 _= 0.90 which will be assessed at one-side significance level *α *= 0.05.

The trial is designed as a two-stage study with a planned interim analysis, allowing for early stopping, and a power of 0.90 to reject the null hypothesis. In the first stage, 15 patients are enrolled. If all these patients would tolerate radiation therapy according to the definition of the primary endpoint, the study would stop with rejection of the null hypothesis. The study would terminate with acceptance of the null hypothesis, if less than 12 of the first 15 patients would tolerate the radiation therapy. According to the current design, the trial would continue with the second stage enrolling further 22 patients, if the number of patients that tolerate radiation therapy is between 12 and 14. In the final analysis, the null hypothesis can be rejected if the product of the one-sided p-values of the two stages is lower or equal to 0.021. With an expected sample size of 21.4 for a tolerability rate of *p*_0 _= 0.70 (i.e., under the null hypothesis), this design shows similar characteristics as Simon's (1989) optimal design whose expected sample size is 21.2. under the same scenario [34]. However, the adaptive two-stage design implemented in this trial allows a data-driven modification of the sample size of the second stage based on the results of the interim analysis or on external information while the specified significance level is controlled when the decision rules defined above are adhered to [35].

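### The aim claims superior tolerability over conventional WAR, but the single-arm primary test can show only that the rate free of CTC grade 4 toxicity exceeds 70%

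*Protocol article*

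**What the plan says.** The Study objectives section opens with a comparative aim: "The aim of the study is to demonstrate superior tolerability of consolidating intensity-modulated WAR compared to the conventional technique". It then turns to historical experience. Acute toxicity of conventional WAR is described in words, and the figures attached to it concern treatment delivery: it "leads in many cases to a stop (10-15%) or to an interruption (15-30%) of the therapy". No CTC grade 4 rate for conventional WAR is printed. The only grade 4 rate in the article, 0 of 10, comes from the preceding phase I study of the intensity-modulated technique.

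The same section sets the primary endpoint on a different scale. Tolerability is "defined by the non-occurrence of CTC grade 4 toxicity during the radiation therapy and until 6 weeks after its termination". Stop and interruption rates are secondary outcomes.

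Statistical Design and Methods gives the benchmark: "The target tolerability rate is 90%, and a tolerability rate of less or equal to 70% is considered to be not of interest". The test of p ≤ 0.70 is one-sided at 0.05. The value 0.70 is presented as a rate without interest, not as the rate seen with conventional WAR. Secondary outcomes are analysed descriptively with 95% confidence intervals.

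Elsewhere the objective has no comparator. The last paragraph of the Background, Duration of the study and the Discussion all speak of showing that tolerance is good.

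**The concern.** A test supports a claim of superiority over a comparator when its null value represents that comparator on the same endpoint. Here the aim names conventional WAR, the historical figures describe stopped or interrupted treatment, and the endpoint counts grade 4 toxicity. These are different events: treatment can be interrupted without grade 4 toxicity, and grade 4 toxicity can arise in the six weeks after treatment has been completed.

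What is at stake is the headline conclusion. If the null hypothesis is rejected, the aim as printed invites the statement that the new technique is better tolerated than the conventional one. That follows only if the conventional grade-4-free rate is 70% or lower, which the article neither states nor supports.

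**Working it through.** **Inputs (Statistical Design and Methods).** p0 = 0.70, p1 = 0.90, one-sided α = 0.05, power 0.90. Stage 1 has 15 patients: reject at 15/15, accept the null below 12, continue at 12 to 14. Stage 2 has 22 patients: reject if the product of the two stage p-values is at most 0.021.

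**Step 1: decision rule.** The stage 1 p-value is P(X ≥ x₁) for X ~ Bin(15, 0.70). The stage 2 p-value may be at most 0.021 divided by it.

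| Stage 1 count | Stage 1 p | 0.021 / p | Stage 2 count needed (of 22) | Total |
|---|---|---|---|---|
| 12 | 0.2969 | 0.0707 | 19 | 31/37 |
| 13 | 0.1268 | 0.1656 | 18 | 31/37 |
| 14 | 0.0353 | 0.5954 | 16 | 30/37 |

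Success after stage 2 is thus possible at 30/37 = 81%.

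**Step 2: reproduce the plan's figures.** For a true rate p, the rejection probability is

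R(p) = P(X₁ = 15) + P(X₁ = 12)·P(X₂ ≥ 19) + P(X₁ = 13)·P(X₂ ≥ 18) + P(X₁ = 14)·P(X₂ ≥ 16),

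with X₁ ~ Bin(15, p) and X₂ ~ Bin(22, p).

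- At p = 0.70: 0.0047 + 0.1700 × 0.0681 + 0.0916 × 0.1645 + 0.0305 × 0.4942 = 0.0047 + 0.0116 + 0.0151 + 0.0151 = 0.0465, within the stated 0.05.
- At p = 0.90: R = 0.904, against the stated power of 0.90.
- Expected sample size at 0.70: 15 + 22 × 0.2921 = 21.43, against the stated 21.4. An exhaustive search for Simon's optimal design gives 21.23, against the stated 21.2.

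The design does what it says for the hypothesis it tests.

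**Step 3: what rejection means for the stated aim.** Assumption: conventional WAR has a grade-4-free rate q over the same window, which the article does not give, and the intensity-modulated technique has exactly that rate. A positive trial read as superiority is then wrong, and it occurs with probability R(q).

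| q | 0.65 | 0.70 | 0.75 | 0.80 | 0.85 | 0.90 |
|---|---|---|---|---|---|---|
| R(q) | 0.012 | 0.046 | 0.15 | 0.36 | 0.66 | 0.90 |

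R rises with p, so for a technique worse than conventional WAR the probability is lower than the value shown.

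**Step 4: can the printed historical figures supply q?** They measure another event, and they do not give a single value even as a stand-in. Free of stop: 100 − 15 = 85% to 100 − 10 = 90%. Free of interruption: 100 − 30 = 70% to 100 − 15 = 85%. Free of both, if no patient has both: 100 − (15 + 30) = 55% to 100 − (10 + 15) = 75%. If every stopped patient is also among those interrupted: 70% to 85%. The article does not say how the two overlap.

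**The case against.** The strongest reply is that the comparative sentence stands alone. The Background, Duration of the study and the Discussion state the objective without a comparator, and Statistical Design and Methods never presents 0.70 as the conventional rate. Testing one arm against a fixed threshold is an accepted phase II design. All of this stands, and it is why the repair is to the claim and not to the design. It does not remove the problem, because the comparative sentence is the stated aim in the section that defines the endpoint.

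A second reply is that a grade 4 benchmark may exist in the full protocol or in the sources cited, which are not shown. That is possible. The point made here is narrower: aim, historical data and endpoint do not fit together as printed.

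Four stronger readings are tempting and not supported:

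- *That a false superiority claim is likely.* A reader might take the values 0.36 to 0.90 as the error rate. They hold only if q is 0.80 or more. The article describes conventional toxicity as frequent and severe, so q at or below 0.70, where the error is 0.046 or less, cannot be ruled out. The 0.90 at p = 0.90 is simply the planned power.
- *That 0.70 was built from the stop and interruption rates.* Adding them to 25-45% assumes that no patient has both, and the article makes no such link.
- *That the phase I data show the endpoint misses the relevant toxicity.* Grade 3 toxicity was 40% there, but the article also reports that treatment was delivered as planned.
- *That the endpoint should be a composite including stops and interruptions.* This is a redesign for which the article supports neither 0.70 nor 0.90 as benchmarks.

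**Conclusion.** The concern holds as a mismatch between the stated aim and what the primary test can show. Rejecting the null hypothesis supports a grade-4-free rate above 70% and nothing comparative. A superiority reading is held near the nominal 5% only if the conventional grade-4-free rate is at most about 70%. Above that, the chance of a misleading positive result for an equally tolerated technique grows from 0.15 at 0.75 to 0.90 at 0.90. These figures rest on an assumed q that the article does not give, and on the decision rule being followed with 15 + 22 patients.

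The two-stage design, its error rates and its expected sample size are correct as stated. Severity is moderate: the issue touches the main conclusion, but it is confined to the comparative claim, and the article already contains the objective that matches the test.

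**What to change.** In Study objectives, restate the aim and the primary conclusion as showing that the proportion of patients free of CTC grade 4 toxicity, from the start of radiotherapy to six weeks after its end, exceeds 70%. Remove superiority over the conventional technique from the primary claim. This brings the section into line with the Background, Statistical Design and Methods, Duration of the study and the Discussion.

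Report the stop and interruption rates, already planned as secondary outcomes with 95% confidence intervals, beside the historical 10-15% and 15-30%. Label this comparison descriptive and non-confirmatory.

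Endpoint, thresholds, sample size and decision rule stay as they are, and no further data are needed. The cost is a less ambitious claim: the trial would no longer announce that it demonstrates an advantage over conventional WAR.

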### Patient selection: Inclusion criteria

Patients meeting all the following criteria will be considered for admission to the trial:

• histologically confirmed ovarian cancer or tube cancer or primary peritoneal carcinoma stage FIGO III

• status post primary optimal debulking surgery

• postoperative gross residual tumor ≤ 1 cm (R0, R1 or R2 < 1 cm situation)

• status post (neo-) adjuvant chemotherapy with platin and taxane

• complete remission after adjuvant chemotherapy (clinically, radiographically and biochemically)

• Karnofsky performance score > 60

• patient >18 years of age

• written informed consent

### Patient selection: Exclusion criteria

• stage FIGO I or II

• stage III with postoperative gross residual tumor > 1cm

• stage FIGO IV

• recurrence situation

• delayed wound healing post laparotomy

• leucopenia <2000/ml before radiotherapy

• thrombocytopenia <75000/ml before radiotherapy

• clinically active renal, hepatic, cardiac, metabolic, respiratory, coagulation or hematopoietic disease

• status post pelvic or abdominal radiotherapy

• status post other cancer disease in the past 5 years (cervical cancer in situ, basal cell carcinoma, squamous cell carcinoma of the skin are excluded)

• participation in another clinical trial

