#### Monitoring during treatment

Patients are evaluated weekly during radiotherapy. Antiemetic and antidiarrheal medications are prescribed as required. Blood count is assessed twice weekly. Toxicities are graded according to the National Cancer Institute Common Toxicity Criteria version 3.0. The quality of life is assessed at the last treatment fraction using EORTC-QLQ30 questionnaire. The documentation of acute hematologic, genito-urinary and gastro-intestinal acute toxicities is especially relevant.

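### Both numeric blood-count exclusion limits are printed per ml, a unit in which neither can exclude any patient; reconcile the unit with the full protocol and the CRF

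*Protocol article*

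**What the plan says.** The article's exclusion criteria (Patient selection: Exclusion criteria) contain two numeric blood-count limits: "leucopenia <2000/ml before radiotherapy" and "thrombocytopenia <75000/ml before radiotherapy". The same list also excludes "clinically active renal, hepatic, cardiac, metabolic, respiratory, coagulation or hematopoietic disease", which is qualitative and names no count.

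No other section repeats the two limits in another unit or gives a minimum count. The baseline visit includes a blood test without unit or limit. The section on monitoring during treatment says only "Blood count is assessed twice weekly".

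The Background section says of consolidation whole abdominal radiotherapy (WAR): "It is associated with a high rate of severe acute side effects, particularly myelosuppression, due to additive toxicities after chemotherapy". For the ten phase I patients treated with the intensity-modulated technique it reports "CTC grade 3 toxicities were: diarrhea (n = 1), thrombocytopenia (n = 1) and leukopenia (n = 3"), and no grade 4 acute effect. The primary outcome under Study objectives is tolerability, "defined by the non-occurrence of CTC grade 4 toxicity during the radiation therapy and until 6 weeks after its termination".

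**The concern.** The digits and the unit do not fit together. Cell counts per ml run to hundreds of thousands at the very least, so limits of 2000 and 75000 per ml lie far below anything a laboratory would report in a living patient. Read literally, the two criteria are inoperative.

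This is operative eligibility text, not background. Every patient enters after platinum and taxane chemotherapy, and the article itself names marrow suppression as a leading acute risk. Of the five grade 3 toxicities listed for phase I, four were haematological (3 leukopenia + 1 thrombocytopenia). The endpoint definition, as given, neither requires that a grade 4 event be attributed to radiotherapy nor adjusts for the baseline value. If a patient with a very low count were admitted, that count could contribute to a recorded failure. At stake are the safety of such a patient and, secondarily, the interpretation of the tolerability rate.

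**Working it through.** **Inputs.** The two printed limits (exclusion criteria). The ratio 1 ml = 1000 microlitres. A range of patient counts, which is an assumption because the article gives none: leucocytes 100 (extreme aplasia) to 10,000 per microlitre; platelets 5,000 to 400,000 per microlitre.

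**Step 1: convert the printed limits.**
- Leucocytes: 2000 per ml ÷ 1000 = 2 per microlitre (0.002 × 10⁹/L).
- Platelets: 75000 per ml ÷ 1000 = 75 per microlitre (0.075 × 10⁹/L).

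**Step 2: compare with the assumed counts.** Multiple = (count per microlitre × 1000) ÷ printed limit per ml.

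| Cell | Assumed count per microlitre | Same count per ml | Multiple of printed limit | Excluded as printed? |
|---|---|---|---|---|
| Leucocytes | 100 | 100,000 | 50 | no |
| Leucocytes | 1,000 | 1,000,000 | 500 | no |
| Leucocytes | 10,000 | 10,000,000 | 5,000 | no |
| Platelets | 5,000 | 5,000,000 | 67 | no |
| Platelets | 25,000 | 25,000,000 | 333 | no |
| Platelets | 400,000 | 400,000,000 | 5,333 | no |

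No count in either range falls below the printed limit. The same digits read per microlitre would exclude the low end of both ranges. That shows the size of the discrepancy only; it does not establish which limit is intended.

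**Step 3: does the statistical design depend on this?** The stated operating characteristics follow from the stage sizes (15 and 22), the rates 0.70 and 0.90, the interim bounds and the product criterion of 0.021. The blood-count limits do not enter.
- Probability of continuing at p = 0.70 with 12 to 14 of 15: 0.29687 − 0.00475 = 0.29212.
- Expected sample size: 15 + 22 × 0.29212 = 21.43 (stated 21.4).
- Exact enumeration of both stages gives type I error 0.0465 (limit 0.05) and power 0.904 (stated 0.90).

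All three agree with the article.

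**Step 4: direction of any bias.** Admitting patients with low baseline counts can only add grade 4 haematological events. That lowers the observed tolerability rate and makes rejection of the null hypothesis harder, not easier.

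**The case against.** The strongest reply is that the slip is self-evident. The criteria speak of leucopenia and thrombocytopenia, so low counts are plainly meant to be excluded, and a clinician would hardly apply a limit of 2 leucocytes per microlitre. The article also condenses an ethics-approved full protocol; that document and the CRF are not shown and may carry the right unit. A micro sign could have turned into an m at typesetting or when the PDF was read. All of this stands. It makes a misprint the likely explanation and harm in practice unlikely. It does not make the printed text correct: the article states a unit, rather than leaving one out, and an eligibility limit should not depend on readers overriding it. The planned second study center makes consistent wording more important.

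Three stronger readings are tempting but unsupported.
- A reader might infer that the trial excludes nobody for haematological reasons. The qualitative exclusion of active coagulation or haematopoietic disease remains in force, although it sets no count and does not clearly cover residual cytopenia after chemotherapy.
- A reader might take 1000 as the distance between the limits and real counts. It is only the ml-to-microlitre ratio; the distance depends on the count assumed.
- A reader might infer that cytopenic entrants will confound the endpoint or decide the interim analysis, since four failures among the first 15 leave fewer than 12 successes and end the trial. The rule is as stated, but the article gives no baseline count distribution, no frequency of cytopenia after chemotherapy and no numeric grade 4 limits. The scenario cannot be quantified.

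**Conclusion.** The point holds for the printed text. In the stated unit, both numeric haematological exclusions are inoperative: assumed counts exceed the limits by factors of 50 to 5000 (leucocytes) and about 67 to 5300 (platelets). The ranges are assumptions, but the conclusion does not change anywhere within them, and extreme aplasia is already included.

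The error is most likely a unit misprint, and no wrong enrolment is shown. It deserves correction because these are the only numeric controls on baseline counts before a treatment with known marrow toxicity and a grade 4 toxicity endpoint. Any effect on the result would be towards a lower tolerability rate. Sample size, type I error and power stand as stated. Whether the error reaches the working documents cannot be judged from the article.

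**What to change.** Reconcile the unit of both limits with the full protocol and the CRF, and correct it wherever eligibility is checked, including any materials for a second center. The sponsor should confirm the intended unit and limit; this review does not propose one. If the same error is found in the full protocol or the CRF, check the baseline counts of patients already enrolled against the confirmed limit and document the outcome. If those documents are correct, a correction to the article is enough.

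The cost is two lines of text and a look at the CRF entry limits, plus a check of baseline counts only if the error has carried over. Sample size and power do not change.
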